### Analysis

#### Sample size

Longitudinal sample size calculation for repeated measures was conducted using a program developed by Hedeker [42]. Previous online interventions targeting distress in community samples have effect sizes ranging from .42 to .65 for depression, and from .29 to 1.74 for anxiety [19]. Therefore, a conservative small-to-moderate effect size was selected for the current study. Based on the pilot RCT findings, an attrition rate of 21% at each of the assessment points can be expected [29]. Thus for a study with 2 groups and 4 assessment points, power set at 0.80, statistical significance set at α = .05 (two tailed), total attrition set at 21%, an effect size set at 0.35 SD, and an expected primary endpoint standard deviation of 4.0 at each time point [43], 94 participants per group are required, summing to a total sample of 188 participants.

#### Statistical analysis

Quantitative data will be analysed using the Statistical Package for the Social Sciences (SPSS) Version 17.0. Baseline differences between groups will be investigated using t-tests for continuous measures and *χ*^2^ tests of independence for categorical measures. Linear Mixed Effects Models (LMEM) will be employed to examine the efficacy of the intervention. The LMEM calculates a regression line for each individual while controlling for baseline observation (fixed main effects). Baseline observations will be entered as covariates to eliminate the influence of baseline variability, resulting in a 2 (group: intervention; control) X 3 (time: post-program; 3-month follow-up; 6 month follow-up) fixed effects model for each outcome variable, with random effects accounting for individual variation. This approach effectively equalises conditions at baseline and consequently allows for direct comparison between conditions at each follow-up point. In this context, (a) interactions between condition and time, (b) main effects of group and (c) post-hoc pairwise comparisons at each follow-up point are all indicators of intervention effects. This analysis offers the benefit of estimation maximisation; it provides joint modelling for each participant of observed and missing data based on maximising likelihood for population parameters as a function of the observed data. LMEM analyses are therefore robust with respect to handling missing data and unbalanced designs in longitudinal research as all participants with at least one observed *post-treatment* data point are included. That is, as baseline data is entered as a covariate, participants who do not complete any of the post-program assessments are not retained. To overcome this limitation and ensure this trial adopts a fully intention-to-treat design, multiple imputation will be performed for participants with only baseline-data. Therefore all participants, regardless of missing data at one or more assessment points, will be included in analyses and accurate parameter estimates obtained. Within-group effect sizes and reliable change indices will be calculated to provide a measure of the magnitude and clinical significance of changes respectively. To test for moderation, separate LMEM analyses will be conducted for each combination of moderator and outcome variable, where the moderator and group are entered in model 1 to control for main effects. The product term is then entered in model 2, to represent the interaction between group and moderating variable, and will indicate the moderating effect.

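### One baseline slope and random effects of unstated form serve all three follow-up comparisons; a baseline-by-time term and an unstructured covariance would be a cheap safeguard

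*Protocol article*

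**What the plan says.** All of this is in the protocol article, under Statistical analysis unless noted.

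- **Baseline term.** It is a covariate, labelled a fixed main effect: "The LMEM calculates a regression line for each individual while controlling for baseline observation (fixed main effects". No product of baseline and time is named.
- **Fixed part.** The adjustment is described as "resulting in a 2 (group: intervention; control) X 3 (time: post-program; 3-month follow-up; 6 month follow-up) fixed effects model for each outcome variable".
- **Dependence within a person.** The only statement is "with random effects accounting for individual variation". Whether this means intercepts, slopes or both is not said, and no residual covariance is given.
- **Claim made for the adjustment.** "This approach effectively equalises conditions at baseline and consequently allows for direct comparison between conditions at each follow-up point".
- **Use of the per-visit contrasts.** Beside the interaction and the main effect of group, "post-hoc pairwise comparisons at each follow-up point are all indicators of intervention effects". The first hypothesis, under Aims and hypotheses, also names post-treatment, 3 months and 6 months.
- **Planning values (Sample size).** "an expected primary endpoint standard deviation of 4.0 at each time point", "an effect size set at 0.35 SD" and "statistical significance set at α = .05 (two tailed". No correlation between time points is given.

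**The concern.** The first follow-up comes seven weeks after baseline and the last six months after treatment ends, which is nearly eight months after baseline. A baseline score often predicts a near measurement better than a distant one. If so, a single slope is an average of the three that are needed: it adjusts too little at post-treatment and too much at 6 months.

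A second issue depends on the form of the random effects. A random intercept with a common residual variance gives every follow-up the same total variance, and hence, with complete data, the same standard error for each per-visit contrast. If the variance left after baseline adjustment differs between visits, that shared standard error is wrong at some of them.

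Both issues concern the per-visit contrasts, which the plan uses as evidence on its primary hypothesis. At stake are the error rate at individual follow-ups and some power at post-treatment.

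**Working it through.** The plan states no standard error or correlation for this model, so there is no figure of its own to reproduce. The check does not depend on whether 94 per group is right.

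**Inputs from the article:** equal SD at each time point (4.0, scaled to 1 below); effect 0.35 SD (0.35 x 4.0 = 1.4 points); two-sided alpha .05; 94 per group, 21% attrition, so 94 x 0.79 = 74.26 per group.

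**Assumed:** baseline/follow-up correlations r1, r2, r3; a random intercept only.

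**Formulas (SD 1 at each visit)**
- Common slope: b = mean of the r_j.
- Residual variance at visit j: v_j = 1 - 2 b r_j + b². With a visit-specific slope it would be 1 - r_j².
- Variance used by the random-intercept model at every visit: p = mean of the v_j.
- Actual type I error at visit j: 2 x [1 - Phi(1.96 x sqrt(p / v_j))].

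**Correlations .7, .5, .4:** b = .533; v = .538, .751, .858; p = .716; visit-specific optimum .51, .75, .84.
- Single-slope cost at post-treatment: .538 / .51 = 1.05, about 5% of variance, or 2.7% in standard error.
- Type I error: 2.4%, 5.6%, 7.3%. Fitting 600 simulated null trials gave 2.5%, 5.3%, 7.2%.
- Post-treatment power: model SE = sqrt(2 x .716 / 74.26) = .139, true SE = sqrt(2 x .538 / 74.26) = .120, so power = Phi((.35 - 1.96 x .139) / .120) = 74%. With the visit-specific slope and variance, SE = sqrt(2 x .51 / 74.26) = .117 and power is 85%. Keeping the single slope but using the correct SE gives Phi(.35 / .120 - 1.96) = 83%, so most of the loss comes from the variance assumption.
- A chance baseline imbalance of 0.2 SD leaves 0.2 x (.7 - .533) = .03 SD uncorrected at post-treatment and 0.2 x (.533 - .4) = .03 SD at 6 months.

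**Correlations .6, .5, .4:** b = .5; v = .65, .75, .85; p = .75. Type I error is 3.5%, 5.0%, 6.6%; post-treatment power is 71% against 76%.

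**Other assumed patterns, random intercept only.** For unequal SDs, r_j is replaced by r_j x SD_j in b and v_j, and the leading 1 by SD_j².

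| Correlations | SDs relative to baseline | Type I error, % (post / 3 mo / 6 mo) |
|---|---|---|
| .65, .60, .55 | equal | 4.0 / 5.0 / 6.1 |
| .70, .60, .50 | equal | 3.0 / 5.0 / 7.2 |
| .75, .60, .45 | equal | 2.1 / 5.0 / 8.3 |
| .60 throughout | equal | 5.0 / 5.0 / 5.0 |
| .6, .5, .4 | 1, .95, .9 | 4.7 / 5.0 / 5.3 |
| .6, .5, .4 | 1, .875, .75 | 6.8 / 4.9 / 3.4 |

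**Simulations with dropout** (7%, 14%, 21% cumulative; correlations .70, .60, .50; 94 per group)
- Random intercept, equal SDs, 1000 runs: model SE .480, .495, .511 points against empirical .449, .488, .579; type I error 3.3%, 4.4%, 9.7%; no bias.
- Random intercept, SDs 4.0, 3.5, 3.0, 500 runs: 6.8%, 3.4%, 5.4%. The excess is now at post-treatment, not at 6 months.
- Random intercept and slope, equal SDs, 200 runs: 5%, 4%, 7%. The Monte Carlo error is sqrt(.05 x .95 / 200) = 1.5 points, so 7% cannot be told from 5%.

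**The case against.** The strongest reply is that the error-rate figures belong to a model the article does not specify. It never says that the random effect is an intercept only. A separate regression line for each person reads more naturally as an individual slope as well as an intercept, and with random slopes most of the distortion goes. The article may also leave the covariance structure to an analysis plan that is not shown, so its absence is not a fault. This stands.

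A reader might infer something stronger: that the plan's standard errors are too wide at post-treatment and too narrow at 6 months, so that it loses power early and exceeds 5% late. The documents do not support that. It needs an intercept-only model and residual variance that rises over follow-up. The equal SD is a sample-size input, not a forecast, and the Background section says that the prevalence of distress falls after the first year, so a shrinking spread is plausible. With a constant correlation and equal SDs nothing is distorted; with falling SDs the direction can reverse.

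A reader might also infer that the follow-up comparisons are biased or materially unadjusted. They are not. A common slope is a valid covariate adjustment in a randomised trial, and what it leaves uncorrected is about .03 SD for a 0.2 SD imbalance, against a target of 0.35 SD.

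What the reply does not remove is that the article itself fixes baseline as a main effect, claims comparability at every follow-up from it, and relies on those comparisons. Nor does it show that the more flexible model does harm.

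**Conclusion.** The point holds as a cheap improvement to the stated model, not as a demonstrated error in the plan.

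- **Single slope.** If the baseline association changes over follow-up, each visit is adjusted slightly imperfectly: up to about 5% of variance at post-treatment under assumed correlations .7, .5, .4. Randomisation keeps the contrasts unbiased. This part does not depend on the form of the random effects.
- **Standard errors.** These are miscalibrated only under added assumptions. With an intercept-only random effect, equal SDs and the declining correlations .7, .5, .4 or .6, .5, .4, type I error is about 2-4% at post-treatment and 6-7% at 6 months. A steeper decline, or dropout, gave higher 6-month values (8.3% and 9.7%); other plausible patterns gave none or the opposite.

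Every correlation used here is an assumption, because the documents give none.

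**What to change.** Replace the model statement with: fixed effects for group, time, group x time, baseline and baseline x time, and an unstructured covariance over the three follow-ups in place of the random effects. Take both the group effect averaged over follow-ups and the comparison at each follow-up from this one model.

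The cost is a few more parameters. Baseline x time adds two. The unstructured covariance has six, against two for a random intercept with a common residual variance and four for a correlated random intercept and slope. The planned 188 participants, or about 148 after 21% attrition (188 x 0.79), support this easily. No new data are needed and the same software can be used. If the baseline correlation and the variances turn out to be constant, the per-visit standard errors are essentially unchanged (0.467 points under either model at a correlation of .60, with 94 per group).

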**Methods/Design:**

The study is a multi-site Randomised Controlled Trial (RCT) seeking to enrol 188 participants who will be randomised to either the *Finding My Way* Intervention or an attention-control condition. Both conditions are delivered online; with 6 modules released once per week, and an additional booster module released one month after program-completion. Participants complete online questionnaires on 4 occasions: at baseline (immediately prior to accessing the modules); post-treatment (immediately after program-completion); then three and six months later. Primary outcomes are general distress and cancer-specific distress, with secondary outcomes including Health-Related Quality of Life (HRQoL), coping, health service utilisation, intervention adherence, and user satisfaction. A range of baseline measures will be assessed as potential moderators of outcomes. Eligible participants are individuals recently diagnosed with any type of cancer, being treated with curative intent, aged over 18 years with sufficient English language literacy, internet access and an active email account and phone number. Participants are blinded to treatment group allocation. Randomisation is computer generated and stratified by gender.

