### Aims and hypotheses

This study aims to evaluate the efficacy of the next iteration of our self-help internet cancer coping intervention (‘*Finding My Way’*) in improving wellbeing and quality of life of early-stage cancer patients over time, using a multi-site RCT.

A secondary aim is to investigate moderators of therapeutic change, consistent with recommendations that RCTs should identify who benefits most, and under what conditions, from psychosocial interventions [30]. For the present study, factors that have been previously shown to predict distress will be examined for their potential to moderate the effects of the intervention; namely, availability of social support, cognitive vulnerability to distress, and motivation to seek information [8,31].

Therefore it is hypothesised that:Intervention participants will report greater improvements compared to attention-control participants in the primary outcome, distress, from baseline to post-treatment and 3- and 6-month follow-up;Intervention participants will report greater improvements compared to attention-control participants in the secondary outcomes coping and HRQOL over time;Primary and secondary outcomes will be moderated such thatThe significant changes over time in distress between groups will be moderated by social support, cognitive vulnerability to distress, and motivation to seek information, andThe significant changes over time in coping and HRQOL between groups will be moderated by social support, cognitive vulnerability to distress, and motivation to seek information.

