#### Primary outcome: distress

The primary outcome for this study is distress, measured as general distress and as cancer-specific distress. General distress is measured using the total scale score of the 21-item Depression Anxiety Stress Scale – short form (DASS: [33]), which assesses levels of anxiety, depression and stress over the previous week on a four-point scale ranging from (0) Did not apply to me at all to (3) Applied to me very much, or most of the time. Cancer-specific distress is measured using the 17-item Posttraumatic Stress Scale-Self Report [34], which measures on a 4-point scale (*0 = Not at all or only one time, 3 = 5 or more times per week / almost always*), the severity of each DSM-IV post-traumatic stress disorder symptom criterion in terms of how often respondents experienced each symptom in the previous week. For this study, the measure was adapted in order to reflect cancer diagnosis as the stressor.

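### Interaction, group main effect and three pairwise tests stand as equal evidence of effect on each of two primary scales, with no confirmatory contrast; if either scale suffices, false-positive risk is well above 5%

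*Protocol article*

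**What the plan says.** **Primary outcome.** The section on the primary outcome states: "The primary outcome for this study is distress, measured as general distress and as cancer-specific distress". The Abstract uses the plural: "Primary outcomes are general distress and cancer-specific distress". The first hypothesis, under Aims and hypotheses, treats distress as one construct and covers all three post-baseline assessments: "in the primary outcome, distress, from baseline to post-treatment and 3- and 6-month follow-up". None of these places says whether one scale or both must succeed.

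**Model.** The Statistical analysis section enters baseline as a covariate and specifies a "2 (group: intervention; control) X 3 (time: post-program; 3-month follow-up; 6 month follow-up) fixed effects model for each outcome variable". It then lists what counts as evidence: first "a) interactions between condition and time", and with it "b) main effects of group and (c) post-hoc pairwise comparisons at each follow-up point are all indicators of intervention effects". It names no primary contrast, primary time point, testing order or adjustment.

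**Level.** The only significance level is in the Sample size section, "statistical significance set at α = .05 (two tailed"), used with "power set at 0.80" for a calculation on a single, unnamed primary endpoint.

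**The concern.** There are two separate problems.

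1. **Multiplicity.** Each scale has one interaction test, one main-effect test and three pairwise tests, so two scales give 2 × 5 = 10. The text gives them equal standing as evidence. If each is read at .05, one significant result among ten could be reported as efficacy, and the chance of that under no effect is well above .05. The Discussion links a finding of efficacy to integrating the programme into supportive care, so it matters which result carries the claim.

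2. **What the interaction tests.** Only the three follow-ups are outcomes. A benefit already present at post-treatment and held constant to six months gives no group-by-time interaction. The interaction asks whether the effect changes across follow-up. It is a poor candidate for the decisive test, and nothing in the text ranks it below the main effect.

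**Working it through.** **Inputs from the article.** Two primary scales; three post-baseline time points; five tests per scale; two-sided α = .05; 94 per group; effect 0.35 SD; attrition 21%; power 0.80.

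**Inputs assumed.** The article gives no correlations. I take a within-person correlation r of 0.5–0.7 (compound symmetry) and a between-scale correlation of 0.3–0.8, and then a wider grid.

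**The plan's own figure.** The article gives no error rate for the set of tests, so there is none to reproduce. Its sample size fits a single test at .05. A single-time comparison needs 2 × (1.960 + 0.842)² / 0.35² ≈ 128.1, that is 129 per group. Averaging four assessments and allowing for attrition multiplies 128.1 by (1 + 3ρ)/4 and divides by 0.79. This equals 94 at ρ ≈ 0.44. So 94 is consistent with the stated inputs, but cannot be confirmed without ρ.

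**Bound.** Ten independent tests: 1 − 0.95¹⁰ = 40.1%. The real tests are correlated, so the rate is lower and has to be simulated.

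**Simulation under no effect on either scale** (400,000 draws per setting). Group contrasts are drawn at three times on two scales. Each scale gets a 2-df chi-square test for the interaction and z tests for the main effect and the three pairwise contrasts, all at two-sided .05. Adjusting for baseline changes the correlation between follow-ups from r to (r − r²)/(1 − r²) = r/(1 + r), so 0.5–0.7 becomes 0.33–0.41. I ran it both with that adjustment and with 0.5–0.7 applied directly to the adjusted values.

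| Rule for a positive result | Chance of a false positive |
|---|---|
| Any of ten tests, either scale, baseline-adjusted correlation | 24–29% |
| Any of ten, 0.5–0.7 applied directly | 23–28% for between-scale 0.3–0.7; lowest corner (0.7 and 0.8) about 22% |
| Any of ten, wider grid (0.3–0.9 over time, 0–0.9 between scales) | 17–30% |
| Pairwise tests only after a significant interaction or main effect, either scale | 15–18%; wider grid 14–19% |
| One scale alone, any of five | about 16% (14–16% with 0.5–0.7 applied directly) |
| Two main effects only, either scale | 8–9.5% |
| Any of five required on both scales | 3–8% |

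**Interaction against a constant benefit.** Take r = 0.6, complete data, and 0.35 SD at every follow-up. Given baseline, each follow-up has variance 1 − 0.36 = 0.64 and each pair has covariance 0.6 − 0.36 = 0.24. The variance of the three-visit mean is (0.64 + 2 × 0.24)/3 = 0.373. The standard error of the group difference is √(2 × 0.373/94) = 0.0891, so z = 0.35/0.0891 = 3.93, and power is Φ(3.93 − 1.96) = 97.5%. All differences between follow-up effects are 0, so the interaction rejects at its nominal 5%. The 97.5% illustrates the contrast between the two tests under complete data and an assumed r; it is not a revised estimate of the trial's power.

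**Cost of controlling two scales.** Set each scale at 80% power (mean z of 1.960 + 0.842 = 2.802). With Hochberg, a scale is positive if its p ≤ .025, or if both p ≤ .05. For between-scale correlation 0.3–0.8, per-scale power is 77–78% if both scales benefit. If only one benefits it is about 71%, close to the Holm first step: Φ(2.802 − 2.241) = 71.2%.

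**The case against.** **No any-of-ten rule is stated.** The sentence can be read as guidance on interpreting the model, and it calls the pairwise comparisons post-hoc. This stands, and it is why the rate is conditional. But the sentence gives no gate and sets the pairwise tests beside the other two. Even with a gate, the either-scale rate is 14–19%.

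**Nothing says that either scale suffices.** The hypothesis concerns one construct. If both scales had to be positive, the rate would be about 3–8%, near or below the nominal level. This also stands. A reader might infer that the trial's false-positive rate simply is 23–28% instead of a promised 5%. The article supports neither half: it states no success rule, and .05 appears only as a sample-size input, not as a family-wise guarantee.

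**Such detail belongs in an SAP.** The adjustment method and the win rule may well be there, and their absence here is not the point. The equal standing of the five tests is stated outright, and an SAP naming one confirmatory contrast would have to override it.

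**The interaction is a legitimate indicator.** A reader might infer that it is no efficacy test at all, or that the plan would dismiss a durable benefit for lack of one. Neither follows. In a randomised, baseline-adjusted comparison, a true interaction means that the arms differ at one or more follow-ups, and the plan lists the main effect alongside it. What remains is that the interaction is a partial indicator, unsuited to be decisive.

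**Conclusion.** The point holds in conditional form. The article gives five tests per scale equal standing on two primary scales and fixes no contrast, order or adjustment. If either scale can carry the efficacy claim, the chance of at least one false-positive indicator is about 23–29% with all ten tests counted (17–30% over the wider grid) and about 14–19% with gated pairwise tests. One scale alone with all five tests gives about 16%. These figures assume the correlations set out above, normal-theory tests each read at .05, and no effect on either scale. Only a both-scales rule brings the rate near 5%, and the article does not state one. Separately, the interaction has no power against a constant, sustained benefit and should not be the confirmatory test.

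**What to change.** Amend the Statistical analysis section, before any comparison of outcomes by arm, to:

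- name one confirmatory contrast per primary scale. The baseline-adjusted group effect averaged over the three follow-ups is one suitable choice and fits the hypothesis of benefit at all three; a single named time point would also be defensible;
- state the rule for the two scales: Holm or Hochberg at an overall two-sided 5% if either suffices, or each at 5% if both are required;
- label the group-by-time interaction as a test of whether the effect changes over follow-up;
- report the three pairwise comparisons as supportive estimates with confidence intervals.

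This changes wording only and needs no extra participants or data. The cost is the Hochberg power loss shown above: from 80% per scale to about 77% if both scales benefit, and to about 71% if only one does. The second loss is not trivial and should be weighed when choosing the rule.

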## Background

Despite improvements in treatment and survival rates, a cancer diagnosis continues to elicit greater distress than any other medical diagnosis [1]. Research has consistently found that 30 to 40 per cent of recently diagnosed patients experience clinically significant depressive or anxiety disorders [2,3]. Distress is most acute during the first 12 months after diagnosis, when a range of medical treatments take place, following which the prevalence reduces to levels comparable with the community [4]. Consequently, distress management within the first 12 months after diagnosis has been recognised as an integral component of a patient’s clinical treatment [5,6]. Despite this, distress and psychiatric disorders among cancer patients often go under-recognised and untreated [7]. This particularly applies to the 30% of Australian cancer patients who reside in rural or regional areas, where access to specialist cancer services is limited [6].

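### Magnitude and clinical significance are assigned to within-group effect sizes and reliable change indices, although the hypothesis, the sizing and the efficacy test are between groups

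*Protocol article*

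**What the plan says.** The hypothesis in Aims and hypotheses is a comparison of arms: "Intervention participants will report greater improvements compared to attention-control participants in the primary outcome, distress". The Sample size section follows it. The calculation is "for a study with 2 groups and 4 assessment points", with "an effect size set at 0.35 SD" and "an expected primary endpoint standard deviation of 4.0 at each time point".

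The Statistical analysis section then sets out a 2 (group) by 3 (time) mixed model with baseline as covariate. It names the group effect, the group-by-time interaction and the pairwise comparisons at each follow-up as the indicators of an intervention effect. Up to here everything is between groups.

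The sentence on magnitude departs from this: "Within-group effect sizes and reliable change indices will be calculated to provide a measure of the magnitude and clinical significance of changes respectively". The section names no standardised difference between arms and no comparison of reliable change between arms.

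Two other places bear on how far the control arm may change. The Background says distress is most acute in the first 12 months after diagnosis, "following which the prevalence reduces to levels comparable with the community". The Attention control section says the authors' earlier research found no significant reduction in distress under such a control.

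**The concern.** An effect size computed inside one arm cannot separate what the programme did from what would have happened anyway. The trial has a control arm so that this separation can be made, and the authors make the same point about their own pilot: it showed moderate pre-post effect sizes in 12 people but could not establish efficacy against a control.

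Two things are at stake. First, the named magnitude measure cannot be set beside the 0.35 SD on which the trial was sized, because the two are different quantities. Second, a reader or meta-analyst looking for the size of the benefit would find a figure that can be above zero when the programme adds nothing to information alone. A reliable-change count read within one arm has the same weakness.

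**Working it through.** **Inputs from the protocol article.** Sample size: effect 0.35 SD, SD 4.0, "power set at 0.80", two-sided 5%, 21% total attrition, 94 per group. Outcomes: post-treatment assessment seven weeks after baseline, then about 3 and 6 months after treatment completion. Participants: in active treatment or, after surgery alone, diagnosed within six months; no distress threshold for entry.

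**Inputs assumed, because the documents give none.** Change common to both arms, c: 0 to 0.5 SD. Correlation between baseline and follow-up, ρ: 0.3 to 0.7. Reliability of the scale, r: 0.85 to 0.90.

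**1. What kind of quantity is the 0.35?** On the stated scale it is 0.35 × 4.0 = 1.4 points. A single two-sample comparison needs 2 × (1.96 + 0.8416)² / 0.35² = 128.1, so 129 per arm, or 129 / 0.79 = 163.3, so 164 after attrition. That is not 94. Averaging four assessments under a common correlation multiplies 128.1 by (1 + 3ρ)/4. At ρ = 0.44 this gives 128.1 × 0.58 = 74.3, and 74.3 / 0.79 = 94.1. A two-group repeated-measures calculation can therefore reach 94 with a plausible correlation. Since the correlation is not stated, 94 is neither confirmed nor refuted. The check serves only to show that 0.35 SD belongs to a comparison of two groups.

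**2. Within-arm against between-arm effect size.** Dividing by the baseline SD:

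- control arm: d = c
- intervention arm: d = c + δ, where δ is the treatment effect
- between arms: (c + δ) − c = δ

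With δ = 0.35:

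| Common change c (assumed) | Control, within | Intervention, within | Between | Intervention / between |
|---|---|---|---|---|
| 0 | 0 | 0.35 | 0.35 | 1.00 |
| 0.20 | 0.20 | 0.55 | 0.35 | 1.57 |
| 0.35 | 0.35 | 0.70 | 0.35 | 2.00 |
| 0.50 | 0.50 | 0.85 | 0.35 | 2.43 |

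With δ = 0 the intervention column equals the control column, 0 to 0.50.

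**3. The standardiser.** If the within-arm change is instead divided by the SD of change, it is multiplied by 1/√(2(1 − ρ)): 0.845, 1.00 and 1.291 at ρ = 0.3, 0.5 and 0.7. A total change of 0.70 then reads 0.59, 0.70 or 0.90. The same data give different effect sizes, and the article does not say which divisor is meant.

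**4. Reliable change.** The usual threshold in SD units is 1.96 × √(2(1 − r)). For r = 0.90 it is 1.96 × 0.447 = 0.877. For normally distributed change, the proportion reliably improved is 1 − Φ((0.877 − mean change)/√(2(1 − ρ))). At ρ = 0.5 the divisor is 1:

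- c = 0: control 19.0%, intervention (δ = 0.35) 29.9%, difference 10.9 points
- c = 0.35: control 29.9%, intervention 43.0%, difference 13.1 points
- c = 0.50: control 35.3%, intervention 48.9%, difference 13.6 points

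Over r = 0.85 or 0.90, ρ = 0.5 or 0.7 and c from 0 to 0.5, the control proportion runs from 8.3% to 35.3% and the difference from 9.2 to 17.3 points. So 29.9% reliably improved in the intervention arm may mean a real effect with no common change, or no effect with c = 0.35. Only the contrast tells them apart.

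**5. Do the documents fix c?** They do not. The Background places the fall in distress after the first 12 months. Seven weeks is about 1.6 months, so the last assessment is about 7.6 months after baseline. For surgery-only participants enrolled 0 to 6 months after diagnosis, that is about 7.6 to 13.6 months after diagnosis, mostly inside the acute period. Participants in active treatment have no stated limit on time since diagnosis, and some may pass 12 months. The Attention control section points towards little change, though a non-significant reduction is not a reduction of zero.

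**The case against.** The strongest reply is that the plan already measures the treatment effect between arms. The mixed model yields the adjusted mean difference at each follow-up, the section calls those comparisons the indicators of intervention effects, and the sentence at issue speaks of the magnitude of changes rather than of the effect. In a two-group trial, within-group effect sizes would naturally be given for both arms, so the control change would be visible. Standardising a model estimate or tabulating reliable change by arm may also be set out in a full protocol or SAP that is not shown. All of this stands, and it limits the point to reporting. It does not remove the point, because the sentence positively assigns magnitude to a within-group measure.

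A reader might infer more than the documents support:

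- *That efficacy itself is judged within groups.* It is not; the test is between arms.
- *That both arms must improve during follow-up, so that the effect is overstated by 1.6 to 2.4 times.* That range results from assuming 0.2 to 0.5 SD of common change and leaving out zero. The Background dates the decline after 12 months, and the Attention control section reports no significant control-arm reduction.
- *That regression to the mean will inflate the figure.* Entry requires no minimum distress score, so eligibility does not select extreme baselines.
- *That the within-group figure will be the headline result, or that reliable change will be reported for one arm only.* Nothing in the article says either.

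**Conclusion.** The point holds as a mismatch between the stated measures of magnitude and clinical significance and the question the trial asks. The hypothesis, sizing and test are between groups; the one named effect size is within group, and no between-arm comparison of reliable change is stated. The within-group figure in the intervention arm equals the between-group effect only if the control arm does not change, and then only with the baseline SD as divisor.

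For a true effect of 0.35 SD the intervention arm would show 0.35 to 0.85 over an assumed common change of 0 to 0.5 SD. No value in that range can be preferred from the documents, and at zero there is no distortion. The primary test, the sample size and the hypotheses are unaffected. This is a modest reporting correction, worth making because it is specific and costs almost nothing.

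**What to change.** Replace the sentence with three statements:

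1. Magnitude is the baseline-adjusted difference between arms from the planned mixed model, divided by the pooled baseline SD, with a 95% CI at post-treatment, 3 months and 6 months.
2. Clinical significance is the proportion with reliable improvement and the proportion with reliable deterioration in each arm, compared as risk differences with 95% CI. The reliability coefficient and the denominator are to be stated.
3. Within-arm effect sizes are shown for both arms, with the divisor named, as description only.

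The cost is a change of wording and a few lines of analysis code. No further data, participants or change to the efficacy test are needed. The drawback for the authors is that the reported effect sizes may be smaller than the within-arm ones.
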